##### Pressures From Different Sources to Drink More and to Drink Less (Baseline and Follow-up)

Two questions on pressures to drink have been adapted from the core questionnaire from the GenACIS project [21], which are as follows: “During the last 12 months, have any of the following persons attempted to influence your drinking so that you would drink less or cut down?” and “During the last 12 months, have you felt influenced to drink or drink more by someone who drinks more than you do?” with each question having the following response options: “Your spouse/partner/romantic partner?” “Your child or children?” “Some other female member of your family?” “Some other male member of your family?” “Someone at your work?” “A female friend or acquaintance?” “A male friend or acquaintance?” and “A doctor or health worker?” with yes or no answer categories for each option.

##### Awareness of Alcohol Harms (Baseline and Follow-up)

As no validated scale currently exists to measure awareness of alcohol harms, 2 questions will be taken from the scale used in the 2017 study by Coomber et al [22]: (1) “Which of the following do you think are likely consequences of a single occasion of heavy drinking (ie, short-term consequences)?” with participants asked to rank the accuracy (ranging from definitely untrue to definitely true) of the following consequences: “Lack of coordination and slower reflexes,” “Reduced concentration,” “Motor vehicle, bicycle and pedestrian accidents,” “Injuries associated with falls, accidents, violence and intentional self-harm,” “Alcohol poisoning,” “Drownings,” “Coma and death,” and (2) “Which of the following do you think are likely consequences of consuming alcohol over many years (ie, long-term consequences)?” with participants asked to rank the accuracy of the following consequences: “Harm to unborn babies,” “Cirrhosis of the liver,” “Brain damage,” “Stomach problems,” “Heart and blood disease,” “Pancreatitis,” “Bowel cancer,” “Pharyngeal cancer,” “Oesophageal cancer,” “Mouth cancer,” “Larynx cancer,” and “Breast cancer.”

##### Drinking Motives Questionnaire (Baseline and Follow-up)

Drinking motives will be assessed using the Drinking Motives Questionnaire-Revised [23].

#### Baseline and Follow-up Survey: Other Measures

##### Readiness to Change (Baseline and Follow-up)

Readiness to change will be measured using the 12-item Readiness to Change Questionnaire [24].

##### Current Level of Stress (Baseline, EMA, and Follow-up)

Current level of stress will be measured using the 4-item Perceived Stress Scale [25].

##### Self-efficacy (Baseline, EMA, and Follow-up)

Self-efficacy will be measured using the 10-item General Self-Efficacy Scale [26].

##### Relationship Quality (Baseline and Follow-up)

Relationship quality will be measured using the second item of the Relationship Assessment Scale [27], “In general, how satisfied are you with your relationship?” with five possible answer categories ranging from 1 (not satisfied) to 5 (very satisfied).

##### Current Health Status (Baseline and Follow-up)

Current health status will be measured using the first item of the General Health Questionnaire [28]— “In general, would you say your health is,” with five possible answer categories ranging from 1 (poor) to 5 (excellent).

##### Mental Health (Baseline and Follow-up)

Mental health will be measured using the 5-item Mental Health Inventory [29].

##### Social Support or Loneliness (Baseline, EMA, and Follow-up)

Social support or loneliness will be measured using the 8-item UCLA Loneliness Scale-8 [30].

##### Current Use of Technology (Baseline)

Five items from the Media and Technology Usage and Attitudes Scale [31] will be used to capture attitudes toward technology. Participants will be asked how strongly they agree with the following questions: “I feel it is important to be able to access the Internet anytime I want,” “I think it is important to keep up with the latest trends in technology,” “I get anxious when I don’t have my cell phone,” “I get anxious when I don’t have the internet available to me,” and “New technology makes people waste too much time.” Participants will also be asked to report how many hours per week on average they spend on their computer (for leisure and for work), on their mobile phone, on a tablet, searching the internet on any device, and using apps on any device.

##### Client Satisfaction Survey (Follow-up)

The 8-item Client Satisfaction Questionnaire Adapted for Online Interventions [32] will be used.

##### Participant’s Use of Intervention (Follow-up)

The intervention’s back-end system will record the number of times participants log in to view the intervention content, and the time they spend on the website each time they log in. It will also record whether participants complete the requested number of follow-up EMAs. These data (number of visits, time spent on website, and number of EMAs completed) will be extracted from the system to assist in assessing the fidelity of the implementation of the intervention.

### Data Management

Participants will complete all assessments and access the intervention online; data will be stored on a secure server based in Australia. Access to the data will be password protected and limited to the members of the research team.

### Data Analysis

The reporting and presentation of this trial will be in accordance with the CONSORT (Consolidated Standards of Reporting Trials) guidelines for randomized controlled trials, and data on screening, refusals, and dropout will be coded and reported on per the guidelines [33]. The comparative analysis will be analyzed in accordance with the intention-to-treat principle and the completers-only framework. Participants will have to sign up to the intervention and complete approximately 30% of the EMA surveys to be considered for inclusion in the analysis; missing data will be handled accordingly. The intention-to-treat analyses’ multiple imputation methods will be used, while completers-only analyses will be conducted on participants providing scores for all measurements.

All data that are collected will be analyzed using statistical software packages such as STATA (StataCorp) and Mplus (Muthén & Muthén). ANOVAs, contrasting the intervention groups against both control groups, will be run, and logistic and linear regression models will be used to determine potential influencing variables. Longitudinal analyses will be conducted to test group differences in EMA assessments over time.

Besides testing the main effects of the intervention, moderating effects of age, drinking status (whether participants are “risky” drinkers according to the Australian Alcohol Guidelines [34]), educational status, and presence of dependent children in the household will be investigated to establish whether specific subgroups are more likely to benefit from the intervention.

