There is a specific need for interventions designed by, and targeted at, middle-aged women for several reasons. Firstly, men and women have different patterns of alcohol use and different motives for consumption [3,8,9]. For example, women are lighter drinkers than men, and use alcohol to experience respite from their traditional female domestic and caring responsibilities. Further, most web-based interventions that are female-centric have been aimed at pregnant women or those of childbearing age, with the content heavily tailored to these specific groups and a particular focus on the harms of alcohol to unborn babies [10,11]. Lastly, it has been shown that tailoring interventions using co-design with a target population is particularly efficacious in ensuring the effectiveness of an intervention or program [12,13]; thus, an intervention designed by and for middle-aged women is likely to have amplified effectiveness.

To our knowledge, there are no web-based interventions targeted specifically at middle-aged women that have been documented in the literature. Our study aims to fill this gap by developing and testing the effectiveness of a web-based intervention in reducing alcohol consumption among women aged 40-65 years. The primary aim of this study is to test the effectiveness of a 3-arm web-based intervention in reducing both the frequency of alcohol consumption as well as the alcohol intake per occasion among middle-aged women. Secondary aims include testing the effectiveness of the intervention in increasing awareness of the long- and short-term harms associated with alcohol consumption, increasing motivation to reduce alcohol consumption, reducing alcohol-related harm, improving reported health status and mental health, and increasing social support. We will also test reactivity to the ecological momentary assessment (EMA) by comparing a control group with weekly assessment to a pre-post control group.

### Hypothesis 1

We hypothesize that by the end of the intervention period, participants in the web-based intervention group will report significantly lower alcohol consumption compared with participants in the pre-post control group (H1).

### Hypothesis 2

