### Procedures

This study is a 3-arm randomized controlled trial of a web-based intervention to reduce alcohol consumption in middle-aged women.

Potential participants responding to an advertisement will be linked to the study website, which will provide them with a brief description of the study and an eligibility screener. Participants who are eligible will be electronically sent an initial consent form with brief information about the study and will be asked to complete the baseline survey. Participants who do not respond to the initial prompt to complete the baseline survey will be sent 3 reminders over 2 weeks. Upon completion of the baseline survey, participants will be randomized into 1 of 3 groups through the back-end platform specifically designed for the intervention, using a computer-generated number allocated to each participant. Participants will then complete a second short consent form that contains information specific to their intervention arm. As with most behavioral interventions, although it is not possible to blind participants to the procedures relating to their own group, they will not be aware of the procedures relating to the other groups. The researchers responsible for analysis will also be blinded. Only 1 member of the research team, who will be the contact point for any participants experiencing technical difficulties or presenting with queries, will be aware of participant allocation, if required to provide support.

The study will include 3 parallel conditions, of which all 3 will complete a baseline and follow-up questionnaire. The intervention design is shown in Figure 1. Beyond that, the 3 conditions will include the experimental condition (web-based intervention and EMA), and 2 control groups (control group 1: baseline and follow-up assessment only, and control group 2: baseline and follow-up assessment plus EMA). They will undertake assessments of their alcohol consumption over an 8-week period, providing EMA measurements of their alcohol consumption on a twice-weekly basis (measuring their daily alcohol consumption retrospectively). Screenshots of the intervention are shown in Multimedia Appendix 1.

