To improve participants’ knowledge and skills to reduce their alcohol use, and to remove environmental constraints, each module will have between 1 and 3 associated *challenges*. The challenges include, for example, an opportunity for participants to write a script for a conversation with a friend or family member on how to say no when offered alcohol, information on alternate activities participants can do to relax, and an opportunity to track how they engage in these activities over a 1-week period.

Participants will be sent reminders to complete their assessments, and upon completion of the assessment, will be redirected back to the intervention content. Participants can complete the intervention content in any order and will have the entire intervention period to access and work through all of the content.

At the conclusion of the trial, participant summaries will be developed and distributed to those participants who request one.

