### Comparator

Participants in control group 1 will not be contacted again until the 8-week follow-up questionnaire. Participants in control group 2 (baseline and follow-up assessment plus EMA) will undertake the web-based repeated measures assessment of their alcohol consumption retrospectively twice a week. After they are recruited and randomized, these participants will be sent a link via text message to a web-based EMA. The assessment on Sunday at 12 PM will ask them about their drinking patterns over the weekend (ie, Thursday afternoon until Sunday morning), and the assessment on Thursday at 12 PM will ask about their drinking patterns during the week (ie, Sunday afternoon until Thursday morning). All participants in the control groups will be given access to the web-based intervention at the completion of the study.

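### The analysis entry rule (sign-up plus about 30% of EMA surveys) conflicts with intention-to-treat and cannot be applied to control group 1, the comparator for H1, H2 and H3a

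*Protocol article*

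**What the plan says.** Under Data Analysis the protocol article states: "The comparative analysis will be analyzed in accordance with the intention-to-treat principle and the completers-only framework". The next sentence sets an entry condition: participants must "sign up to the intervention and complete approximately 30% of the EMA surveys to be considered for inclusion in the analysis". It is not limited to an arm or to one of the two analysis sets.

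The same paragraph then gives each analysis set its own handling. For intention-to-treat, "multiple imputation methods will be used"; separately, "completers-only analyses will be conducted on participants providing scores for all measurements". The 30% condition is therefore not the definition of completers.

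The Procedures section places randomization directly after the baseline survey, before any EMA. It gives control group 1 baseline and follow-up assessments only. The Comparator section confirms this: "Participants in control group 1 will not be contacted again until the 8-week follow-up questionnaire". It also says the control groups get access to the web-based intervention only once the study is over.

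H1, all of H2, and H3a use control group 1 (the pre-post group) as comparator. The Data Analysis section plans ANOVAs comparing the intervention with each of the two control groups.

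**The concern.** An intention-to-treat set is fixed by randomization. A condition on later behavior replaces it with a set selected by engagement. Here the condition also cannot be met, or even measured, in one of the three arms.

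What is at stake is the primary comparison. If low-engagement women are removed from the intervention arm and their counterparts stay in control group 1, a difference at 8 weeks may reflect who was kept and not what the intervention did. H2 and H3a are exposed in the same way. In the intervention arm the filter is also tied to exposure, because after each survey participants, "upon completion of the assessment, will be redirected back to the intervention content".

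**Working it through.** **1. The plan's own figures.** Sample Size Calculation: 3000 × 2/3 × 2/3 = 1333, as stated, so 1333 / 3 ≈ 444 per arm. The stated power of more than 99% at α = .001 is reproduced by a noncentral F test with N = 1333, 3 groups, 2 measurements, and two assumed inputs: Cohen f = 0.10 and pre-post correlation 0.5. Then λ = 1333 × 0.01 × 2 / 0.5 = 53.3, with 2 and 1330 degrees of freedom, and power is 0.9999. The point below does not depend on this figure.

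**2. What the threshold means.** Twice weekly for 8 weeks gives 16 surveys; 0.30 × 16 = 4.8, about 5. Four surveys are 25% and five are 31%, so an approximate 30% does not settle the cut-off.

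**3. Applying the rule by arm.**
- Intervention: 16 surveys offered; the rule can be applied.
- Control group 2: 16 surveys offered; the rule can be applied.
- Control group 1: 0 surveys offered; the rule cannot be met.

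Two readings follow. Literally, control group 1 contributes nobody, which contradicts the planned contrasts with both control groups. Applied to the EMA arms only, H1, H2 and H3a each compare a filtered arm with an unfiltered one. Imputation works on women admitted to the analysis, so it does not restore those the rule shut out. The contrast of intervention with control group 2 can apply the rule to both sides, but still conditions on behavior after randomization.

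**4. Illustration of size (assumptions, not document figures).** True effect zero; standardized outcome; latent engagement normal; correlation r with the analysed outcome of 0.1, 0.2 or 0.3 in absolute value; least engaged 30% of the intervention arm dropped; control group 1 unfiltered.

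Shift in the retained mean = r × φ(c) / 0.70, where c is the 30th percentile (−0.524) and φ(c) = 0.348. So the shift is r × 0.348 / 0.70 = 0.497 r.

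Retained numbers: 0.70 × 444 ≈ 311 against 444. SE = √(1/311 + 1/444) = 0.0739 SD.

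| r | Spurious difference (SD) | Difference / SE | False positives, two-sided 5% | At .001 |
|---|---|---|---|---|
| 0.1 | 0.05 | 0.67 | 10% | 0.4% |
| 0.2 | 0.10 | 1.34 | 27% | 3% |
| 0.3 | 0.15 | 2.01 | 52% | 10% |

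The .001 column is shown because that is the only threshold the article states, in its power calculation.

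**5. Sensitivity.** With 90% retained and r = 0.1 the shift is 0.02 SD; with 50% retained and r = 0.3 it is 0.24 SD. If change from baseline is analysed, what matters is the difference between engagement's correlation with follow-up drinking and its correlation with baseline drinking. If the two are equal, and the SDs are equal, selection moves both means alike and the shift in change is zero.

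**The case against.** The article plainly intends to analyse control group 1: its hypotheses name that arm and its ANOVAs include it. A reader might infer that H1 cannot be tested at all. That follows only from a literal reading that the same section contradicts, so it should not be the headline. This stands.

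The sentence may have been meant for the longitudinal EMA analyses, where a minimum number of surveys is natural, and signing up may simply mean joining the trial. Both are possible. The text says neither, and the EMA condition alone is enough to create the conflict.

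A reader might also infer that the rule favors the intervention, on the view that engaged women drink less or cut down more. Nothing in the document supports a direction. The planned power model is a pre-post interaction, in which a correlation with drinking level largely cancels. The article also expects one-third attrition; if disengaged women in control group 1 skip the 8-week questionnaire, the observed outcomes there are selected too, and the imbalance shrinks. These points limit the size of the bias. They do not restore the randomized comparison.

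Finally, the second, arm-specific consent after randomization ("Participants will then complete a second short consent form that contains information specific to their intervention arm") might look like another arm-dependent loss. The article does not say that women who decline it leave the analysis, so this is not a documented defect.

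**Conclusion.** The point holds as a contradiction in the stated rule, not as a detail left for the analysis plan. The protocol promises intention-to-treat and, in the next sentence, makes entry depend on behavior after randomization that one arm cannot show. On the plausible reading (EMA arms only), H1, H2 and H3a are no longer compared as randomized.

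The bias is a risk of unknown sign and size. The illustrated false-positive rates of 10% to 52% at two-sided 5% (0.4% to 10% at .001) rest entirely on the assumed 30% exclusion, the assumed correlations, a true effect of zero and 311 against 444 women. They would be smaller if engagement relates similarly to baseline and follow-up drinking and change is analysed. Since the article itself expects small effects, a shift of even 0.05 to 0.15 SD would matter. This should be settled before the data are analysed.

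**What to change.** Define the intention-to-treat set as all randomized women, in the arm to which they were randomized, regardless of sign-up or EMA completion, where consent permits use of their data. Impute missing 8-week outcomes by multiple imputation over this full set.

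Confine the 30% threshold to a labelled secondary or engagement analysis of the two EMA arms, and state it as a whole number of surveys out of 16. The section on participants' use of the intervention already records EMA completion as a fidelity measure, so no new data are needed. The clause on missing data can stay; only the scope of the entry rule has to change.

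Cost: a documented amendment, since the article reports that recruitment has begun; more imputed outcomes in the primary analysis; and possibly a smaller estimated effect. No change to the sample size follows.

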**Methods:**

The study is a 3-arm randomized controlled trial with a web-based intervention plus ecological momentary assessment (EMA) group compared to an EMA-only and a pre-post only control group. The study is aimed at middle-aged women, defined as women aged between 40 and 65 years, who consume alcohol at least weekly or who have consumed 4 or more drinks on 1 occasion in the last month. The intervention aims to reduce alcohol consumption through 4 modules that provide information on the health impacts of alcohol, mindfulness, social influences, and alcohol marketing. Intervention participants will also fill out biweekly EMA assessments. The comparators are EMA-only and pre-post control only. The primary outcome is alcohol consumption at 8 weeks compared between groups. Secondary outcomes are awareness of alcohol-related harms, readiness to change alcohol consumption, health status, mental health, and social support.

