## Methods

### Study Design

This study is a 3-arm randomized controlled trial including 1 intervention group, 1 pre-post control group and 1 control group with weekly assessment. The trial was registered with Australia New Zealand Clinical Trials Registry (ACTRN12620000814976) on August 14, 2020.

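### Read literally, the completers-only rule demands 2 assessments in the pre-post control but about 18 in each EMA arm, so its contrasts with that control compare differently selected women

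*Protocol article*

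**What the plan says.** The Data Analysis section names two frameworks for the comparative analysis: intention-to-treat, with multiple imputation, and completers-only. It defines the second: "completers-only analyses will be conducted on participants providing scores for all measurements". The sentence is the same for every arm, and nothing in it limits the requirement to baseline and follow-up.

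The assessment schedule differs by arm:

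- **All arms.** Procedures: "The study will include 3 parallel conditions, of which all 3 will complete a baseline and follow-up questionnaire".
- **Control group 1 (pre-post).** Comparator: "Participants in control group 1 will not be contacted again until the 8-week follow-up questionnaire".
- **Control group 2 (EMA-only).** Comparator: these women "will undertake the web-based repeated measures assessment of their alcohol consumption retrospectively twice a week".
- **Intervention arm.** The abstract says "Intervention participants will also fill out biweekly EMA assessments". Procedures describes assessment "over an 8-week period, providing EMA measurements of their alcohol consumption on a twice-weekly basis".

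The EMAs measure the outcome itself: in Measures, daily alcohol consumption is listed for baseline, EMA and follow-up alike. One label disagrees with the twice-weekly schedule. Study Design speaks of "1 pre-post control group and 1 control group with weekly assessment".

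**The concern.** EMA completion happens after randomization and exists in only two of the three arms. If a completer must have every EMA, those two arms keep only their most persistent responders, while control group 1 keeps everyone who returns one follow-up questionnaire. Women who answer every text-message prompt for 8 weeks may well drink differently from those who miss a few. A completers-only difference from control group 1 could then reflect who was kept rather than what they received.

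H1, H2 and H3a all compare an EMA arm with control group 1. H3a is the most exposed, because it asks whether EMA itself changes drinking and the rule selects on compliance with EMA. The completers-only result stands beside the intention-to-treat result, and the article does not rank the two, so a distorted one could falsely support or contradict the other.

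**Working it through.** **Inputs from the article.** EMA twice a week for 8 weeks (Procedures, Comparator); baseline and follow-up in all arms (Procedures); recruitment target of 3000, a possible shortfall of one-third and attrition of one-third (Sample Size Calculation). The article gives no completer count and no EMA response rate.

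**The article's own figure.** 3000 × 2/3 × 2/3 = 1333, as stated. Split equally over three arms, 1333 / 3 ≈ 444 women per arm with follow-up.

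**Assessments required by the literal rule.**

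- Control group 1: 1 baseline + 1 follow-up = 2.
- Intervention and EMA-only: 2 + (2 × 8) = 18.
- If the weekly label were right: 2 + 8 = 10. The imbalance shrinks but remains.

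Randomization follows the baseline survey, so after randomization the requirement is 1 assessment against 17.

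**Women kept in each EMA arm (assumed response rates).** Among the 444 with follow-up, the share with all 16 EMAs is as follows.

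| Assumption | Share with 16/16 | Kept of 444 |
|---|---|---|
| 98% per EMA, independent | 0.98^16 = 0.724 | about 322 |
| 95% per EMA, independent | 0.95^16 = 0.440 | about 196 |
| 90% per EMA, independent | 0.90^16 = 0.185 | about 82 |
| 90% mean, beta-binomial, ICC 0.3 | 0.582 | about 258 |

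For the last row, a + b = (1 − 0.3)/0.3 = 2.333 and a = 0.9 × 2.333 = 2.1. The probability is the product of (2.1 + i)/(2.333 + i) for i = 0 to 15. Control group 1 keeps about 444 in every row.

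**Shift in drinking level with no treatment effect.** Suppose women are kept when a normally distributed completion propensity exceeds a cut-off, and that propensity correlates r with drinking. The mean shift among those kept is r × φ(z)/p, where p is the share kept and z the matching normal quantile.

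- r = 0.2, p = 0.582: 0.2 × 0.3905 / 0.582 = 0.13 SD.
- r = 0.2, p = 0.185: 0.2 × 0.2672 / 0.185 = 0.29 SD.

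A variant lets ordinary one-third attrition select on the same propensity in all arms and takes the difference from control group 1. It gives 0.07 to 0.19 SD at 95% response and 0.11 to 0.33 SD at 90%, for r = 0.1 to 0.3. The direction follows the sign of the correlation.

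**Change instead of level.** If propensity correlates r0 with baseline and r1 with follow-up drinking, and the SDs are equal, the shift in change is (r1 − r0) × φ(z)/p. With r1 = r0 it is zero.

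**Contrasts affected.** H1, H2 and H3a set 18 requirements against 2. Intervention versus EMA-only sets 18 against 18.

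**The case against.** The strongest reply is that the rule may have been meant more narrowly. Sample Size Calculation describes the group comparison as two measurements over time, pre and post, and mentions EMA separately. The voucher rule in Procedures treats finishing the study as completing the final assessment. On that reading a completer already has the same two assessments in every arm. This is possible, but the article does not say it. The voucher sentence governs only the prize draw, Procedures itself calls the EMAs measurements ("providing EMA measurements of their alcohol consumption on a twice-weekly basis"), and Measures lists them among the occasions for daily alcohol consumption. The rule is stated, and stated badly; it is not a detail left to another document.

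Other objections stand and limit the point:

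- **Level or change.** The SD shifts apply to drinking level. The power calculation is for a pre-post interaction, where a selection effect that is stable over time would largely cancel. Data Analysis says only that ANOVAs will be run, so a follow-up-only comparison is not excluded.
- **Data lost.** A reader might infer that the rule discards most follow-up data in the EMA arms. That holds at 90% independent response (82 of 444 kept) but not with clustering (258 of 444 kept), and clustering within a woman is the more plausible case.
- **Role of the analysis.** An intention-to-treat analysis with multiple imputation is planned alongside. The article nowhere makes completers-only primary.

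The same section also requires about 30% of EMAs for inclusion in the analysis. That is a separate rule; removing it would leave the completer definition as it is.

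**Conclusion.** The point holds for the rule as written: 2 assessments against about 18 (10 if the weekly label is right), affecting the completers-only contrasts with control group 1 in H1, H2 and H3a. The count comes from the article's schedule and needs no assumption beyond the literal reading.

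The consequences do need assumptions: a 90% response per EMA for the 18% to 58% retained, and a correlation of 0.2 between completion and drinking for the 0.1 to 0.3 SD in level. A reader might go further and infer a bias of that size in the planned pre-post test, or in the trial's main result. The article does not support either. The first would need completion to correlate with change in drinking, for which there is no figure, and the second overlooks the parallel intention-to-treat analysis. Nor does this imbalance touch intervention versus EMA-only, although engagement could still differ between those arms. The definition should be corrected before analysis.

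**What to change.** Replace the completer sentence in Data Analysis with definitions tied to each analysis:

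1. For the three-arm pre-post comparisons, a completer in any arm is a woman with the baseline and 8-week follow-up outcome measures. EMA completion plays no part.
2. For the longitudinal EMA analyses, which involve only the intervention and EMA-only arms, state a separate EMA completeness requirement and apply it equally to both. Without this, step 1 alone would leave those analyses with no completer definition.
3. Report EMA completion as adherence in the two EMA arms. The intervention's back-end system already records it (Participant's Use of Intervention).

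The weekly and twice-weekly descriptions of EMA should be reconciled at the same time, so that the number of scheduled EMAs is fixed.

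The cost is a sentence or two of text. No new data are needed, and unless every woman answers every EMA, more women stay in the three-arm completers-only comparison: about 444 per arm under the article's own shortfall and attrition.
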